**Discussion:**

This study is designed to evaluate the efficacy of IMPACT compared to nonsurgical care. Additionally, safety of IMPACT will be assessed in 30 to 60 patients. Lastly, this study will evaluate the cost-effectiveness of IMPACT compared to nonsurgical care.

**Trial registration:**

NL67161.000.18 [Registry ID: CCMO]

2018#003470#27 [EU-CTR; registered on 26 March 2019]

NCT04236739 [ClinicalTrials.gov] [registered after start of inclusion; 22 January 2020]

## Administrative information

Note: the numbers in curly brackets in this protocol refer to SPIRIT checklist item numbers. The order of the items has been modified to group similar items (see http://www.equator-network.org/reporting-guidelines/spirit-2013-statement-defining-standard-protocol-items-for-clinical-trials/).

## Introduction

### Background and rationale {6a}

Cartilage defects are common knee injuries that lead to a deterioration of sports performance, increased work leave, and limitations in daily activities. Cartilage defects may eventually lead to osteoarthritis (OA) due to the limited healing capacity of cartilage [1, 2]. Treatment aims at obtaining a pain-free joint function by achieving structural tissue repair. Small cartilage defects are successfully treated using microfracture, but treatment of large defects (2–8 cm^2^) requires more advanced techniques. The application of fresh allografts for large or deep defects is limited by the high costs and poor availability [3]. Synthetic implants are easy to use and short-term results look promising, but the quality of the repair tissue is poor [4, 5]. Autologous chondrocyte implantation (ACI) is a two-stage treatment, in which a biopsy of healthy cartilage from a non-weight bearing location in the knee is taken during an initial knee arthroscopy. Approximately 180,000–455,000 chondrocytes are isolated from such a biopsy [6], while millions of cells per milliliters of defect filling are needed [7, 8]. In order to obtain sufficient chondrocytes to repair the cartilage defect, a period of cell expansion is required [6]. After approximately 4–13 weeks, the cultured autologous chondrocytes are re-implanted into the cartilage defect in a second surgical procedure. Although ACI procedures showed good mid-term and long-term results [9, 10], chondrocyte expansion leads to a decrease in type II collagen and increase in type I collagen gene expression, which are both signs of dedifferentiation [11, 12]. Furthermore, ACI is a costly procedure due to the requirement of cell culture [13] and it has been unavailable in many European countries after different products have been withdrawn from the European market [14, 15]. Due to this limited availability, nonsurgical care consisting of physiotherapy and pain medication remains the treatment of choice.

Both in vitro and in vivo cartilage formation has been shown to improve by direct contact between multipotent mesenchymal stromal cells (MSCs) and articular chondrocytes [16–20]. This stimulatory effect on cartilage matrix formation further increases when MSCs are combined with chondrons (chondrocytes with their pericellular matrix) [19]. Using this combination of cells allows for a one-stage application, as autologous cells can be used without expansion. “Instant MSC Product accompanying Autologous Chondron Transplantation” (IMPACT) combines 10% autologous chondrons with 90% allogeneic MSCs in a single surgery for the treatment of cartilage defects. Compared to the two-stage ACI procedure, IMPACT decreases the patient burden and significantly reduces the costs of treatment [13]. Safety, feasibility, initial efficacy, and structural tissue repair of IMPACT was shown in a cohort of 35 patients with cartilage lesions (3.2 ± 0.7 cm) (NCT02037204) [21, 22].

### Objectives {7}

The current phase III randomized controlled trial explores the efficacy of IMPACT compared to nonsurgical care in 60 patients with large (2–8 cm^2^) articular cartilage defects of the knee. We allow patients in the nonsurgical group to cross-over to the IMPACT group after 9 months of nonsurgical care. Follow-up will be at least 18 months after IMPACT. The primary objective is to compare the Knee Injury and Osteoarthritis Outcome Score (KOOS) at 3, 6, and 9 months follow-up. The secondary objective of this study is to examine morphology and proteoglycan content of repair tissue 6 and 18 months after treatment. Safety endpoints will be determined by the number of (treatment-related) adverse events. In addition, the incremental cost-effectiveness ratio (ICER) of IMPACT vs. nonsurgical care and vs. delayed surgical intervention will be calculated. More specifically, the effect of IMPACT compared with nonsurgical care and delayed surgical intervention in terms of healthcare resource use, productivity losses, and accompanying costs during the study period will be determined and extrapolated to a 5-year time horizon.

### Additional consent provisions for collection and use of participant data and biological specimens {26b}

A subgroup of 15 patients will be asked to participate in an optional study, in which the structure and composition (glycosaminoglycan content) of the regenerated tissue are studied using high-resolution imaging. These patients will undergo additional MRI-scans using a 7-Tesla MRI-scanner at baseline, 6, and 18 months. Regardless of treatment allocation, patients can volunteer for this part of the trial by indication on the informed consent form.

### Trial design {8}

In this phase III randomized controlled clinical trial, IMPACT is compared to nonsurgical treatment. The patient allocation ratio is 1:1. Patients in the nonsurgical group are allowed to cross over to the treatment group after 9 months follow-up.

## Methods: participants, interventions, and outcomes

### Study setting {9}

The IMPACT-trial will be performed in a tertiary referral hospital (University Medical Center Utrecht (UMC Utrecht)) in the Netherlands that is specialized in the treatment of cartilage defects of the knee. Patients are recruited at the Mobility Clinic, which includes the outpatient clinic of orthopedics, sports medicine, and rheumatology and is part of the UMC Utrecht. Patients are considered for inclusion if they meet the criteria as defined below.

### Eligibility criteria {10}

#### Primary inclusion criteria (at the outpatient clinic)

Patients must meet the following criteria to be eligible for the study:
The patient provides written informed consent, is able to understand the content of the study, understands the requirements for follow-up visits, and is willing to complete the questionnaires and provide the required information at follow-up visits.Symptomatic articular cartilage defect of the knee (femoral condyles or trochlea) 2–8 cm^2^.Age ≥ 18 and ≤ 45 years old.

#### Primary exclusion criteria (at the outpatient clinic)

If the patients meet any of the following criteria at the screening visit, they will not be eligible for the study:
Malalignment of > 5° (correctional osteotomy is allowed during the trial).(History of) OA, defined as Kellgren-Lawrence grade ≥ 3 as determined from appropriate radiography.Joint instability (ligament reconstruction is allowed during the trial).Concomitant inflammatory disease that affects the joint (rheumatoid arthritis, metabolic bone disease, psoriasis, gout, symptomatic chondrocalcinosis).(History of) Septic arthritis.(History of) Total meniscectomy in the target knee joint.Any surgery in the index knee joint 6 months prior to study inclusion.Risk groups for MRI due to the magnetic field such as patients with pacemakers, nerve stimulators, metal particles, stents, clips or implants, (possible) pregnancy, or breastfeeding.

Definitive eligibility is assessed during surgery based on the criteria below.

#### Definitive inclusion criteria (during surgery)

Patients must meet the following criteria to be eligible for IMPACT:
Modified Outerbridge Grade III or IV isolated cartilage lesion of the knee.A post-debridement size of the cartilage lesion ≥ 2 cm^2^ and ≤ 8 cm^2^.At least 50% of functional meniscus remaining. Meniscal repair or resection is allowed during the IMPACT surgery provided that the surgeon is able to confirm that at least 50% of functional meniscus remains.Stable knee ligaments (i.e., anterior and posterior cruciate ligaments).

#### Definitive exclusion criteria (during surgery)

Patients who meet any of the following criteria at surgery will not be eligible for IMPACT:
Patients with lesions > 8 cm^2^.Patients with osteoarthritic lesions Kellgren-Lawrence grade ≥ 3 not diagnosed before surgery.

### Who will take informed consent? {26a}

Patients with an MRI- or previous arthroscopically confirmed isolated articular cartilage lesion will be screened for eligibility to participate in this study based on the abovementioned criteria. After the patient has been assessed as eligible by the treating orthopedic surgeon, he/she will receive initial study information. After at least 2 weeks of reflection, patients are invited to meet with the research physician to discuss any remaining questions and sign the informed consent.

## Interventions

### Intervention description {11a}

IMPACT is a one-stage cell-based regenerative therapy for isolated articular cartilage lesions. The investigational product consists of 10% autologous chondrons recycled from the debrided defect tissue and 90% allogeneic MSCs in Tisseel® tissue glue (Baxter B.V, Utrecht, the Netherlands) which will act as a cell carrier for implantation. The MSCs are obtained from the bone marrow of healthy non-HLA matched donors in the GMP-licensed Cell Therapy Facility (Department of Clinical Pharmacy, University Medical Center Utrecht) and cultured and characterized as described previously [22]. To summarize, the bone marrow aspirate is density-separated and MSCs are isolated using plastic adherence. The MSCs are expanded up to passage three after which they are cryopreserved. MSCs are characterized by the expression of CD73, CD105, and CD90 and the absence of expression of CD45, and CD3.

IMPACT surgery [21, 22] consists of a mini-arthrotomy, during which the cartilage defect is debrided and stable borders are created. The debrided cartilage tissue is transported to the Cell Therapy Facility, where chondrons are isolated from the tissue using a rapid digestion protocol; minced cartilage is digested in 40 min in Liberase MNP-S GMP Grade (Roche, Mannheim, Germany). The autologous chondron-suspension is run over a 100-μm strainer (Corning Inc., New York, USA) to remove the undigested cartilage matrix. The chondrons are washed twice to remove the enzyme and counted using 3% acetic acid with methylene blue (STEMCELL Technologies Germany GmbH, Köln, Germany). Allogeneic cryopreserved MSC are thawed and the chondrons and MSCs are mixed at a 10:90 ratio in the fibrinogen component of Tisseel®. The fibrinogen and thrombin component of Tisseel® are mixed upon application, which causes the product to gelate. Two million cells per milliliter are implanted in the defect. The rehabilitation protocol we use is equal to that after ACI. Briefly, during rehabilitation, patients are allowed 10% weight-bearing the first 3 weeks, after which the load is increased gradually up to 50% at 6 weeks and 100% at 8 to 12 weeks. From 5 months onward, the rehabilitation protocol aims at improving coordination, increasing muscle strength, and becoming functional in moderately intensive activities. Patients can return to low-impact sports after 9 months and to high-impact sports at the earliest after 12 months. Patients treated for cartilage defects in the trochlea are allowed weight-bearing in the first 6 weeks after surgery but will use an extension brace in order to limit the flexion while weight-bearing.

### Explanation for the choice of comparators {6b}

The control group receives standard care, which is nonsurgical. Due to the varying availability of ACI in the Netherlands, this is the comparator of choice for cartilage defects of 2–8 cm^2^. The control group is allowed the option to take pain medication at their own discretion as well as physical therapy by their own physical therapist.

### Criteria for discontinuing or modifying allocated interventions {11b}

Patients can leave the study at any time for any reason if they wish to do so without any consequences. The patient’s participation in this study can also be ended by the investigator if the patient is uncooperative and/or does not attend study visits. The patient data that have been collected up to that moment will be included in the analysis. In case too many data are missing (e.g., missing baseline or all of the follow-up patient-reported outcome measures (PROMs), study visits, or MRI-scans), the patient will be replaced by a new patient. This study will be prematurely ended in case of any abundance in adverse events or procedure/compound-related complications or if the independent rheumatologist advises this termination. Criteria for study termination include any suspected unexpected serious adverse reaction (SUSAR) or serious adverse event (SAE) based on an allergic reaction and clear allergic or iatrogenic effects in two or more patients including patients which report back to the hospital with serious iatrogenic complaints. In case of premature ending, all included patients will be informed by their treating orthopedic surgeon. In case of illness, patients will be asked to contact the primary investigator. Patients that are discovered during surgery not to meet the criteria will not receive IMPACT and will be treated according to the standard of care, based on the findings during surgery. These patients will be removed from the study. Patient data included up to that moment will be included in the analysis.

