### Plans to promote participant retention and complete follow-up {18b}

The patients will receive extensive information about the study set-up and requirements during the recruitment. The importance of completion of the follow-up will be stressed. Patients are allowed to stop at any time during the study and are not obliged to give a reason to discontinue. If possible, the patient will be asked to complete the online survey at 9 months after inclusion. Questionnaires are completed using an online survey, and therefore patients can do this at any convenient moment. All patients are reminded throughout the study to fill out the questionnaires during study visits. Throughout the follow-up period, the researchers will check responses and if necessary contact patients for completion of their follow-up.

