### Methods in analysis to handle protocol non-adherence and any statistical methods to handle missing data {20c}

The primary outcome will be assessed using an intention-to-treat analysis. Missing data will be reduced to a minimum by using the appropriate measures described above. Mixed models do not require imputations for missing data. If any statistical method is needed to account for missing data in the secondary outcomes, multiple imputation will be used.

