### Limitations

There are several limitations to consider. First, cartilage defects may lead to major disability with a high patient burden; therefore, patients are likely to request immediate surgical treatment. The possible delay of surgical treatment by allocation to the nonsurgical control group might impair patient inclusion or increase drop-out in the control group. Risk of drop-out will be minimized by properly informing the patients of the study set-up and goals. Secondly, we compare IMPACT surgery to nonsurgical therapy instead of ACI surgery. A nonsurgical control group was explicitly chosen due to the limited availability of ACI in Europe in the last decade. A comparison with ACI can be made retrospectively using our prospective registry, which includes data on safety, efficacy, and treatment and societal costs of the patients treated with ACI at our center. In addition, to the best of our knowledge, no randomized controlled trial has been performed previously that compares cell therapy to conservative treatment. Lastly, the follow-up period after surgery is relatively short (1.5 years) and long-term efficacy remains to be investigated. We ask permission of all patients to contact them after the study period in order to investigate long term follow-up and aim to include all patients in our prospective registry.

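### Ending participation for missed visits, and asking patients who stop only for the 9-month survey, can forgo 3-, 6- and 9-month KOOS that the online survey could still collect

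*Protocol article*

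**What the plan says.** Section {11b} of the protocol article allows patients to leave at any time. It adds that a patient's "participation in this study can also be ended by the investigator if the patient is uncooperative and/or does not attend study visits". The next sentence reads: "The patient data that have been collected up to that moment will be included in the analysis".

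Section {18b} deals with patients who choose to stop: "If possible, the patient will be asked to complete the online survey at 9 months after inclusion". It mentions no 3- or 6-month request for them, and it does not say whether patients ended by the investigator are included. The same section says "Questionnaires are completed using an online survey, and therefore patients can do this at any convenient moment", and that during follow-up "the researchers will check responses and if necessary contact patients for completion of their follow-up".

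On the outcome and its analysis, section {7} states: "The primary objective is to compare the Knee Injury and Osteoarthritis Outcome Score (KOOS) at 3, 6, and 9 months follow-up". Section {20c} states: "The primary outcome will be assessed using an intention-to-treat analysis". It relies on a mixed model without imputation for that outcome. Section {17a} says that patients, researchers and surgeons are not blinded. The Limitations section says that allocation to the control group "might impair patient inclusion or increase drop-out in the control group".

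**The concern.** Attending a visit and answering KOOS are separate acts in this trial. A patient who misses a check-up can still fill in the survey at home. Section {11b} nevertheless makes missed visits, or an undefined lack of cooperation, a ground for ending participation altogether, and the person deciding knows the allocation. Section {18b} recovers one of the three primary time points for patients who stop, and only where possible.

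At stake are primary-outcome values that the trial could obtain with a system it already runs. An intention-to-treat comparison depends on outcome data from everyone randomised, whether or not they keep to the visit schedule. The mixed model uses what was recorded before a patient stopped. It is valid if the missing scores are what the recorded ones would predict. A control patient who leaves out of dissatisfaction with waiting, or an IMPACT patient who stops attending because the knee is doing badly or very well, may not fit that assumption. Before month 3 the model has only the baseline score to predict from.

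**Working it through.** **1. The plan's own figure.** Inputs from section {14}: SD 15, correlation 0.7, difference 10, power 0.8, alpha 0.05, stated minimum 44.

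- Variance of a change from baseline: 2 × 15² × (1 − 0.7) = 135.
- Patients per arm: 2 × (1.960 + 0.842)² × 135 / 10² = 21.2, rounded up to 22, so 44 in total.
- A Hotelling-Lawley test of group by time over four time points (0, 3, 6 and 9 months), equal correlations, and a 10-point difference at every follow-up also gives 44 (power 0.807).

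The 44 reproduces. The present point concerns data collection and does not change it.

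**2. What is requested after a stop.** Setting {11b} and {18b} side by side:

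| Situation | 3 months | 6 months | 9 months |
|---|---|---|---|
| Patient stops at month 2 | not requested | not requested | requested, if possible |
| Patient stops at month 4 | already due | not requested | requested, if possible |
| Investigator ends participation at month 2 | not requested | not requested | not expressly covered |
| Investigator ends participation at month 4 | already due | not requested | not expressly covered |

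**3. Opportunity to miss a visit, from Table 1 in section {13}, up to month 9.**

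- IMPACT, in person: preoperative screening, surgery/day 1, week 1, week 4, month 6. That is 5 contacts, or 3 if the two that belong to receiving the operation are left out.
- Control, in person: month 6. That is 1 contact.
- Both arms have a telephone check-up at month 3 and questionnaires only at month 9.

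The ratio is 5 to 1 or 3 to 1, depending on the count. Either way, a rule triggered by non-attendance has more occasions to operate in the IMPACT arm. The drop-out named under Limitations would act in the control arm.

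**4. Size of a possible bias.** Let p be the share of an arm with no score at a time point, and let s be the number of points by which the true unobserved scores fall below the model's prediction. The arm mean is then overestimated by about p × s. With the same s in both arms, the error in IMPACT minus control is

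(p_IMPACT − p_control) × s.

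The article gives neither p nor s, so the values below are assumptions. With 60 patients at 1:1 there are 30 per arm.

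| Loss, control vs IMPACT | s = 5 | s = 10 | s = 15 |
|---|---|---|---|
| 20% vs 5% | 0.15 × 5 = 0.75 | 0.15 × 10 = 1.5 | 0.15 × 15 = 2.25 |
| 30% vs 10% | 0.20 × 5 = 1.0 | 0.20 × 10 = 2.0 | 0.20 × 15 = 3.0 |
| 10% vs 10% | 0 | 0 | 0 |

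The entries are absolute sizes in KOOS points at a time point with that loss. If control leavers are worse than predicted, the IMPACT benefit is understated; if they are better than predicted, it is overstated. In the first row the bias is 7.5% to 22.5% of the 10-point target (0.75/10 to 2.25/10). Where the requested 9-month survey is returned, that score is not missing and the loss at month 9 is smaller.

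**The case against.** The case on the other side has several parts.

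- **The 9-month score is requested.** A reader might infer that all three primary scores are lost for everyone who stops. Section {18b} says otherwise: patients who stop are asked for the last primary time point. Loss of all three is arguable only for patients whom the investigator ends before month 3. This stands and limits the point.
- **Later data are not barred.** A reader might take {11b} to mean that only data up to the stop are used. The sentence says that such data are included; it does not exclude what comes later. Read with the 9-month request and intention-to-treat, a returned survey would naturally be analysed. This also stands. A condensed article may leave that detail to the full protocol.
- **The rule is permissive and there is active chasing.** The investigator may end participation but need not, and researchers check responses and contact patients. This makes loss less frequent. It does not help once participation has been ended.
- **Unequal loss is not shown.** Limitations says that drop-out might increase among controls, gives no rate, and adds that informing patients will reduce the risk. Missed visits would act mainly on the other arm, so the two could partly offset. Surgery elsewhere before month 9 is a tempting explanation for control drop-out, but the article does not mention it. What stands is a named risk, not a fact.
- **The margin from 44 to 60 is not a drop-out rate.** It is (60 − 44)/60 = 26.7%, but section {14} says that it also covers uncertainty about the correlation and the standard deviation. It cannot be read as expected loss.
- **The mixed model keeps earlier scores.** It does, and if the remaining loss is explained by them there is no bias.

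None of this gives a reason for missed visits to stop an online questionnaire.

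**Conclusion.** The point holds as a weakness in two stated rules. Section {11b} does not separate ending visits from ending collection of KOOS, and {18b} asks patients who stop for one of three primary time points. Obtainable 3- and 6-month scores can be lost, and 9-month scores too for patients ended by the investigator.

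Whether this biases the result depends on two things that the article does not settle: that the loss depends on unobserved KOOS, and that its effect differs between the arms. Under the assumed 20% versus 5% loss and a 5- to 15-point deviation, the bias is 0.75 to 2.25 points; under 30% versus 10% it is 1.0 to 3.0. It is zero when losses and deviations are equal. These figures show scale and are not forecasts. The change is worth making because it is cheap and protects the primary outcome, not because a bias has been demonstrated.

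**What to change.** In section {11b}, state that missed visits or lack of cooperation do not by themselves stop the online questionnaires. The investigator may still end visits; that decision should be kept separate from outcome collection.

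In {11b} and {18b}, state that every randomised patient who stops visits or allocated care is still sent the 3-, 6- and 9-month surveys, whoever made the decision, unless he or she withdraws consent to contact or data collection. State that the answers enter the intention-to-treat analysis.

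This alters no treatment rule and leaves the sample size as it is. The cost is small changes to protocol and consent wording and a few more reminders through the existing survey system. Some patients will not answer, and those who refuse contact will still be missing.
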